### Study design

2.2

Prospective, unicentric, randomized, double-blinded study in patients with esophageal cancer and esophagectomized by the Ivor-Lewis or McEwan techniques. The study will be carried out in accordance with the good clinical practice in our hospital.

All participants will receive a lipid emulsion by continuous infusion in addition to EN support for 5 days post-surgery. The standard EN support will be initiated with Impact Neutre 500 ml (a normocaloric, hyperproteic and immunomodulatory diet composed of 3.9 g of lipids in each 100 ml, 1.8 g of MCT/100 ml, 0.61 g of ω-6 fatty acids/100 ml and 0.6 g of ω-3 fatty acids/100 ml, with a caloric input of 144 kcal/100 ml daily); it will be initiated at 21 ml/h and titrated to 1500 ml daily. When the body mass index (BMI) is greater than 25, the ideal adjusted body weight will be applied following the formula: “Ideal adjusted body weight = ideal body weight + (actual body weight - ideal body weight) ∗ 0.25 (if BMI 26–30) or ∗0.5 (if BMI > 30)”.

Group A will receive a lipid emulsion mixture of 0.4 g/kg/d of fish-oil and 0.4 g/kg/d of LCT/MCT, Group B will receive 0.8 g/kg/d of fish-oil lipid emulsion and Group C will receive a lipid emulsion mixture of 0.8 g/kg/d of LCT plus MCT 50% (view at Fig. 1, which illustrates the diagram flowchart of this study)

**Figure 1 F1:**
[figure not shown]
Study design flow chart.

This study will be conducted in accordance with Good Clinical Practice and this protocol follows the Standard Protocol Items: Recommendations for Interventional Trials (SPIRIT) checklist (Fig. 2 and Additional file 1, which shows the suitability of this study with the SPIRIT guidelines, Supplemental Digital Content).

**Figure 2 F2:**
[figure not shown]
Standard Protocol Items: Recommendations for Interventional Trials (SPIRIT) flowchart.

#### Study population

2.2.1

Patients diagnosed with esophageal cancer and candidates for EPG by the Ivor-Lewis or MacEwan techniques, and who meet the following **inclusion criteria**:

1.18 years old or older, any gender and any race.2.Willing and able to give their written informed consent (IC) for the study. If a subject is unable to give written IC, his legal representative may do so in his/her place.3.Having access to the digestive tract.

Patients who meet the following **exclusion criteria** will not be chosen:

1.Hypersensitivity type 1 or idiosyncratic reactions to any of the lipid emulsion components.2.Pregnant or breastfeeding women.3.Plasmatic triglycerides concentration >3 mmol/L.4.In receipt of chronic treatment with corticosteroids or immunosuppressants in the last month.5.HIV diagnosis.6.Transplanted.7.Hepatic impairment classified as Child-Pugh grade B (significative functional compromise) or grade C (decompensated disease).

##### Subject and/or treatment withdrawal criteria

2.2.1.1

Patients can voluntarily refuse to continue in the study at any time. In addition, presentation of any adverse effect related to the treatment will lead to a treatment withdrawal and to exclusion from the study.

All patients who present with surgical complications classifiable as grade IV of the Dindo-Clavien classification^[18]^ will be excluded from the study.

#### Patients recruitment, randomization and allocation

2.2.2

All patients allocated for EPG following medical criteria, and those who meet the inclusion criteria will be candidates to participate in the trial.

The surgical team will be responsible for communicating the possibility of participating in this trial when IC is obtained for the surgical intervention. IC for participation in this trial will be collected before randomization.

Subjects will be randomized to 3 groups (1:1:1) by a pharmaceutical researcher after recruitment by the surgical team:

Group A will receive 0.4 g/kg/d of fish-oil LE and 0.4 g/kg/d of a LE mixture LCT/MCT receiving a total dose of 0.8 g/kg/d of LE over 5 days post-surgery,Group B will receive 0.8 g/kg/d of fish-oil LE,And Group C will receive 0.8 g/kg/d of a LE mixture of LCT/MCT 50%.

This allocation will be blind for all patients and health personnel. The allocation sequence (computer-generated random numbers) will be generated by the pharmaceutical researcher and it will be performed by randomized blocks permutated with the block size defined at random. In the first step, blocks of size 3 with possible sequences ABC, ACB, CAB and CBA, and size 6 will be defined. In a second step the clusters will be randomized, and in a third step the sequences will be randomized within the blocks. This method ensures that the groups are balanced throughout the study, and that the researcher cannot predict the sequence. The pharmaceutical researcher will be responsible for patient assignation to the corresponding intervention group, and will also assign a numbered patient identification code for each patient in the trial. The composition of the emulsion administered to each patient will only be known by: the pharmaceutical researcher responsible for clinical trials, the pharmaceutical researcher who will validate its conduct, and the personnel who will conduct it.

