#### Number of participants subjects and trial duration:

2.2.3

Recruitment will last a total of 24 months from the approval date. Each subject will participate in the trial for a year post-surgical intervention.

On the basis of the results obtained and as referenced by Furukawa et al^[19]^ (a study of the values of IL6 in esophagectomized patients who received parenteral nutrition with ω-6 fatty acids or without lipids), and considering that the effect of administration of fish-oil emulsion (with ω-3 fatty acids) will be similar to the non-administration of ω-6 fatty acids, a sample size of 33 patients is estimated for 80% of potency and 5% of alfa error with 10% of anticipated losses.

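### The sequences listed for blocks of 3 omit BAC and BCA, so as written Group B can never open such a block and the claim of an unpredictable sequence is weakened

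*Protocol article*

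**What the plan says.** Section 2.2.2 (Patients recruitment, randomization and allocation) sets the ratio and the order of events: "Subjects will be randomized to 3 groups (1:1:1) by a pharmaceutical researcher after recruitment by the surgical team". On the method it says that "it will be performed by randomized blocks permutated with the block size defined at random". The first step is then specified as "blocks of size 3 with possible sequences ABC, ACB, CAB and CBA, and size 6 will be defined", followed by "In a second step the clusters will be randomized, and in a third step the sequences will be randomized within the blocks". The section closes with two claimed properties: "This method ensures that the groups are balanced throughout the study, and that the researcher cannot predict the sequence".

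Nothing marks the four sequences as examples. BAC and BCA appear nowhere in the article, and the orderings for blocks of 6 are not listed. Section 2.2.3 plans 33 patients.

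**The concern.** In permuted-block randomisation with equal allocation, all balanced orderings of a block are normally equally likely, so that each patient has the same chance of each arm whatever the place in the block. The article states a set of possible orderings that leaves out every ordering starting with B. Under that set, a patient who opens a block of 3 cannot be allocated to Group B, the arm in which all the study lipid is fish oil and on which the dose comparison in section 2.1 depends.

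Two things are at stake. Group B is enrolled slightly later within such blocks than Groups A and C. And the stated assurance about prediction is weaker than it reads, because one arm can be excluded with certainty at the start of a block of 3 by anyone who knows the set and can tell that such a block is starting.

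**Working it through.** **Inputs.** From section 2.2.2: three groups, ratio 1:1:1, block sizes 3 and 6 chosen at random, listed size-3 sequences ABC, ACB, CAB, CBA. From section 2.2.3: 33 patients. Assumption: sequences within the stated set are equally likely, since the article gives no weights.

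**Count of sequences.** 3! = 3 × 2 × 1 = 6: ABC, ACB, BAC, BCA, CAB, CBA. The article gives 4. The missing two are BAC and BCA.

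**Chance of each arm by position** (number of sequences with that arm in that place, divided by the number of sequences):

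| Position | A (four listed) | B (four listed) | C (four listed) | Each arm (all six) |
|---|---|---|---|---|
| 1 | 2/4 = 0.50 | 0/4 = 0.00 | 2/4 = 0.50 | 2/6 = 0.33 |
| 2 | 1/4 = 0.25 | 2/4 = 0.50 | 1/4 = 0.25 | 2/6 = 0.33 |
| 3 | 1/4 = 0.25 | 2/4 = 0.50 | 1/4 = 0.25 | 2/6 = 0.33 |

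**Mean position in the block.**
- A: (1 + 1 + 2 + 3)/4 = 1.75
- B: (2 + 3 + 3 + 2)/4 = 2.50
- C: (3 + 2 + 1 + 1)/4 = 1.75
- All six sequences: 2.00 for every arm

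**Overall share.** Each listed sequence contains one A, one B and one C, so each arm has exactly 1/3 of every completed block.

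**Predictability.** Take an observer who knows the block boundaries, the sequence set and the past allocations, and always makes the best guess. The expected number of correct guesses is the sum of the best-guess probabilities at the three positions.
- Four listed: 1/2 + 1/2 + 1 = 2.00 of 3 (66.7%)
- All six: 1/3 + 1/2 + 1 = 1.83 of 3 (61.1%)

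The gain is 0.17 per block and comes entirely from the first position. If every block were of size 3, 33 patients would make 11 blocks, with 11 × 2.00 = 22.0 correct guesses against 11 × 1.83 = 20.2. That is an upper bound, because the plan mixes in blocks of 6.

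**Dilution by blocks of 6.** With all 6!/(2! × 2! × 2!) = 90 balanced orderings allowed (an assumption, since none is listed), B opens a block of 6 with probability 1/3. If a proportion s of blocks is of size 3, B opens a block with probability s × 0 + (1 − s) × 1/3.
- s = 1: 0
- s = 0.5: 1/6
- s = 0: 1/3

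**The case against.** The strongest reply is that the sentence is an incomplete transcription. The section speaks of computer-generated random numbers and permuted blocks, and its third step randomises sequences within blocks, all of which fits ordinary full permutation. This may be what happened. But the text presents the four as the possible sequences, and nothing in it restores the other two. The reply therefore bears on which correction is needed; it does not remove the need for one.

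The second reply concerns size, and most of it stands. The surgical team recruits and is not given past allocations, patients and health personnel are blinded, section 2.4.1 describes identical presentation of the emulsions, and block size varies at random. The pharmaceutical researcher who generates the list knows it whichever sequences it uses. So the figure of 2.00 against 1.83 describes an unusually well-informed observer. The shift in enrolment order is also small. Group B comes 2.50 − 1.75 = 0.75 of a place later, and the shift restarts with each block. Over 24 months (section 2.2.3) that is 0.75 × 24/33 = 0.55 months. Over about 48 months (section 4 dates, read as day/month) it is 0.75 × 48/33 = 1.09 months. Both are somewhat less once blocks of 6 are mixed in.

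A reader might also infer that allocation is not 1:1:1. It is: every listed sequence has one of each arm, so the totals and the balance at the end of each block are exact. Only the chance by position is unequal, and only in blocks of 3.

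**Conclusion.** The point holds in limited form. The randomisation rule as written is wrong for blocks of 3: four of six orderings are given and B has probability 0 at the first position. The claim of balance stands. The claim that the sequence cannot be predicted is weakened, by at most 0.17 correct guesses per block of 3.

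This rests on the listed set being complete and its members equally likely. The predictability figure further assumes an observer with full knowledge of boundaries, sequences and earlier allocations. Random blocks of 6 and blinding make the practical effect smaller.

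A reader might go further and conclude that the trial was in fact randomised from four sequences, so that the usual tests rest on a randomisation that did not take place. The article does not support that. It shows a description, not the generated list.

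**What to change.** State that blocks of 3 use all six permutations (ABC, ACB, BAC, BCA, CAB, CBA) with equal probability and that blocks of 6 use all 90 balanced orderings with equal probability. Then check the generation record.

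- If all six were used, correct the sentence in section 2.2.2. The cost is one line.
- If only four were used, generate the unallocated part of the list from all six, starting at a block boundary so that balance is kept, and report which patients were allocated under the restricted set. The cost is one re-run of the list generator, with the pharmacy record updated by the unblinded staff, and a short statement in the report. If allocation is already complete, only the reporting remains.

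A sensitivity analysis adjusting for enrolment order is optional. With about 33/3 = 11 patients per arm and a shift of less than one place, it is unlikely to add much.

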#### Number of participants subjects and trial duration:

2.2.3

Recruitment will last a total of 24 months from the approval date. Each subject will participate in the trial for a year post-surgical intervention.

On the basis of the results obtained and as referenced by Furukawa et al^[19]^ (a study of the values of IL6 in esophagectomized patients who received parenteral nutrition with ω-6 fatty acids or without lipids), and considering that the effect of administration of fish-oil emulsion (with ω-3 fatty acids) will be similar to the non-administration of ω-6 fatty acids, a sample size of 33 patients is estimated for 80% of potency and 5% of alfa error with 10% of anticipated losses.

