Due to their iso-osmolarity, intravenous administration of lipid emulsions (LE) does not require a central line thereby avoiding any extra invasive treatment for the patient. In fact, LE may have protective properties for the vascular wall. Moreover, in patients considered for the study, the LE could be administered simultaneously with EN, so that gastrointestinal tract stimulation will not be interrupted, and the caloric goal achieved.

Studies of ω-3 fatty acids administered parenterally in esophagectomized patients are poorly reported in the literature. This study proposes to investigate the effect of combining fish-oil lipid emulsions administered parenterally with EN support in the framework of a randomized clinical trial. The difference between this approach and previous published studies is 2-fold:

-Parenteral administration facilitates fast incorporation of lipids to the cellular membranes, and consequently to the inflammatory cascade.^[16]^-Use of only 1 parenteral pharmaconutrient (ω-3 fatty acids) facilitates the caloric goal and enables the study of the immunomodulatory effect of 1 nutrient without interference from other nutrients. When immunonutrition is administered enterally, the commercialized products available are combinations of different immunonutrients. Lipid emulsion comprising combined long-chain ω-6 long-chain fatty acids (LCT) and medium-chain fatty acids (MCT) is proposed as a control lipid to compare the effects on immunomodulation. These emulsions have the same physical appearance as ω-3 lipid emulsion. The LCT emulsions have an active role in the immunological system but are sensitive to peroxidation, whereas MCT emulsions do not participate in the immune response and are not sensitive to peroxidation, so in consequence the combination of both has no immunomodulatory effect.^[17]^

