### Study objectives

2.1

The main objective of this study is:

To establish if the endovenous administration of ω-3 fatty-acid fish-oil lipid emulsions for 5 days in esophagectomized patients is effective in reducing inflammation – measured as seric concentration of interleukin-6 (IL-6) – compared to the administration of lipid emulsions of LCT/MCT. Additionally, to determine if doses of 0.8 g/kg/d are more effective than doses of 0.4 g/kg/d in the normalization of IL-6.

The secondary objectives aim to determine if the intravenous administration of ω-3 fatty-acid fish-oil lipid emulsions for 5 days in esophagectomized patients shows differences compared with the administration of LCT/MCT lipid emulsion with regard to:

Seric concentration of other inflammatory parameters: C-reactive protein, tumoral necrosis factor-α (TNF-α), interleukin-10 (IL-10), interleukin-8 (IL-8) and soluble interleukin-2 receptor. In addition, in the follow-up, whether these markers, alone or in combination, show equal or greater efficacy of effect on the inflammatory response compared to IL-6.Post-operative complications: suture dehiscence, chylotorax, pneumonia and other infections.Safety, measured as hepatic impairment and alterations in coagulation parameters.Nutritional parameters: albumin, prealbumin and lymphocytes.Mortality: evaluated at hospital admission and at 1 year post-surgical intervention.

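### The single 80% power figure was built on a lipid-versus-no-lipid contrast and does not cover the 0.8 versus 0.4 g/kg/d comparison that the main objective also contains

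*Protocol article*

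**What the plan says.** Section 2.2.3 (number of participants) of the protocol article states that "a sample size of 33 patients is estimated for 80% of potency and 5% of alfa error with 10% of anticipated losses". The effect comes from "a study of the values of IL6 in esophagectomized patients who received parenteral nutrition with ω-6 fatty acids or without lipids". It is carried over to this trial by "considering that the effect of administration of fish-oil emulsion (with ω-3 fatty acids) will be similar to the non-administration of ω-6 fatty acids". The article gives no IL-6 difference, SD, test or named pair of groups.

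Section 2.1 (study objectives) has two parts in the main objective. The first is fish oil against LCT/MCT on IL-6. The second is "to determine if doses of 0.8 g/kg/d are more effective than doses of 0.4 g/kg/d in the normalization of IL-6".

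Sections 2.2 and 2.2.2 define three arms at 1:1:1. Group A gets 0.4 g/kg/d fish oil plus 0.4 g/kg/d LCT/MCT, Group B gets 0.8 g/kg/d fish oil, and Group C gets 0.8 g/kg/d LCT/MCT. Section 2.6.1 plans two-group tests between arms.

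The Introduction justifies LCT/MCT as control on the ground that LCT is active and MCT is not, "so in consequence the combination of both has no immunomodulatory effect". It also describes ω-3 fatty acids as reducing proinflammatory cytokine production.

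**The concern.** A reader who finds one power figure for the trial will apply it to the whole main objective. The planning contrast has two levels, ω-6 lipid or none. Group A sits between those levels because it still receives half the control lipid and only half the fish oil. B versus A is therefore not the contrast behind the 80%. If the dose comparison comes out non-significant, the stated 80% invites the reading that the two doses are equivalent, when the trial may have had little chance of separating them.

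The premise raises a second question. Taking fish oil as equivalent to withholding ω-6 locates the planned difference in what ω-6 lipid does to IL-6. The Introduction describes the ω-6-containing control as having no net effect. The two statements pull against each other, and the effect size depends on which one the sponsor holds.

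**Working it through.** **Inputs.** N = 33, power 80%, alpha 5% and losses 10% (section 2.2.3); allocation 1:1:1 (section 2.2.2); two-group tests (section 2.6.1). Sidedness is not stated, so I take two-sided. I work in SD units because the article gives no difference or SD.

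**The plan's own figure.** Without a difference and SD, 33 cannot be derived forward. The loss allowance can be checked: 30 × 1.10 = 33, and 33 × 0.9 = 29.7, so about 10 evaluable per arm. (Dividing 30 by 0.9 gives 34, a trivial difference.) The figure of 33 is not shown to be wrong.

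**Effect implied by 80% power, 10 v 10.**
- Normal approximation: d = (1.960 + 0.842) × √(2/10) = 2.802 × 0.447 = 1.25 SD.
- Noncentral t, 18 df: d = 1.325 SD.

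**B versus A under proportional dose (my assumption).** Each dose step carries half the B–C difference.
- Normal approximation: 0.6265 / 0.447 = 1.401, and power = Φ(1.401 − 1.960) = Φ(−0.559) = 28.8%.
- Noncentral t at 0.6625 SD: 28.9%. The same figure applies to A versus C.

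**Other dose-response shapes.** Here the B–C difference is 1.325 SD, and Group A achieves a given share of it (t test, 10 per arm):

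| Share reached by Group A | Power B v A | Power A v C |
|---|---|---|
| 0 (no effect at 0.4) | 80% | 5% |
| 25% | 56% | 11% |
| 50% (proportional) | 29% | 29% |
| 75% | 11% | 56% |
| 100% (plateau at 0.4) | 5% | 80% |

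For both steps to have 80% power, B–C would have to be 2 × 1.325 = 2.65 SD, twice the effect implied by the plan.

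**Other readings of how 33 was reached, still at half effect for B v A.**
- One-sided 5%, 10 v 10: 34.4%.
- Three-group F test with equally spaced means (f = 0.60, B–C = 1.47 SD): 34.3% with a two-sample t test, 35.3% with pooled error, 37.5% by normal approximation.
- Pooled fish oil (20) versus control (10), d = 1.124 SD: 22% if 1.124 is taken as the B–C effect. Under proportional dose the pooled contrast is 0.75 of B–C, so B–C = 1.124 / 0.75 = 1.50 SD and power is 35.5%.
- Two arms of 15: d = 1.06 SD, power 20%.

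The range is about 20-38%, with 29% for the plain two-sided pairwise reading.

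**What the dose comparison can deliver.** The 95% confidence interval for B–A with 10 per arm has a half-width of about 2.101 × 0.447 = 0.94 SD. A null result would therefore not exclude the 0.66 SD half effect. For scale, 80% power at half effect needs about 40 evaluable per arm by the normal formula (37 by the t test). At 40 per arm, 40 / 0.9 rounds up to 45, or 135 randomised.

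**The case against.** The sponsor could fairly say that section 2.2.3 never claims 80% for the dose question. Section 2.3 defines the main variable only as fish oil against LCT/MCT, and section 2.1 attaches the dose question as an addition. Sizing on the leading contrast is common. That stands as an explanation of how the number arose. It does not remove the mismatch, because section 2.1 still lists the dose comparison under the main objective and the article gives no other power statement.

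Four stronger readings are tempting and are not supported:
- *The planning assumption itself implies about 29% power for the dose question.* It does not. The 29% needs proportional dose-response, which the protocol does not state; other shapes give anything from 5% to 80%.
- *The expected fish-oil effect is zero because the control is neutral.* That would follow only if fish oil were literally no more than an absence of ω-6. The Introduction gives ω-3 its own active mechanism, and section 2.2.3 can be read as borrowing only a magnitude. A neutral control is then compatible with a real difference.
- *Enteral ω-6 dilutes the contrast.* The enteral formula supplies "0.61 g of ω-6 fatty acids/100 ml and 0.6 g of ω-3 fatty acids/100 ml" under the same regimen in every arm. A common background cancels from an additive between-arm difference, and the documents state no interaction or saturation.
- *33 is a miscalculation.* The article does not give the difference or SD, and a condensed article commonly leaves them to the full protocol.

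**Conclusion.** The point holds in a limited form. The 80% was calculated for a two-group contrast and cannot be read as the power of the whole main objective. The dose comparison was not sized. Its power is about 29% if the effect is proportional to dose, about 20-38% across the sizing readings above, and 80% only if Group A has essentially no effect, in which case A versus C has almost none. For any dose-response in which Group A lies between C and B, the effect that gives B versus C its 80% cannot give 80% to both steps.

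These figures assume about 10 evaluable patients per arm, two-sided 5% unless noted, and an effect back-solved from the plan's own N, power and alpha. They do not depend on the missing IL-6 values. The conflict over whether the control is neutral is a real tension in the text that needs resolving; it does not show that the trial has no effect to find.

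**What to change.** Keep 33 patients and change the wording:
1. In section 2.2.3, state that the 80% applies only to the fish-oil versus LCT/MCT comparison actually used in the calculation, and name that comparison.
2. In sections 2.1 and 2.2.3, say that 0.8 versus 0.4 g/kg/d will be reported as an estimated difference with a confidence interval. Give its lower power with the dose-response assumption behind it, and say that a non-significant result will not be read as equivalence of the doses.
3. Reconcile the Introduction with section 2.2.3 on whether LCT/MCT is taken as neutral or as raising IL-6. Say also that the borrowed contrast is ω-6 lipid against no lipid, not fish oil against LCT/MCT.

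The cost is rewording only, with no added patients or procedures. The downside is a less favourable stated power for the dose question.
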